### **10.3.3 Family characteristics and demographic measures**

*T1 sample description, process evaluation.*

Parents will provide information about their child's age and sex, their own sex, their own and their child's ethnicity, parental education and employment and relationship status and whether there are other children with neurodevelopmental difficulties living in the household. We will estimate family socioeconomic status based on total household income, coded as < £16,000 | £16,000 - £29,999 | £30,000 - £59,999 | > £60,000 | Prefer not to say.

### **10.3.4 App usage data**

*During intervention period, intervention arm only. App use up to T2 as post-randomisation effect modifier for the primary SNAP ODD outcome at T2 and secondary ODD outcome at T5, process evaluation.*

To establish intervention adherence, the number of completed modules will be measured (min = 0; max = 8), with completion of two modules constituting adherence to the intervention. Other collected app usage events will include: the number of started modules, the number of videos watched, and the time spent watching videos (in seconds), the number of audio clips listened to and the time spent listening to audio clips (in seconds), the number of reflections recorded, the number of items saved to favourites, and the number of accessed text resources. These will be used to provide descriptive information about app usage patterns. The format of the app usage data is being finalised as part of the feasibility study, so we are not yet able to specify the app usage variable(s) up to T2 that will be used as the effect modifier. Likely options include: the number of started modules or total time engaging with the app. We will aim to specify this in a future protocol amendment, and/or the statistical analysis plan.

### **10.3.5 Clinical diagnosis**

*Risk ratio at T5 as exploratory outcome.*

Information about ADHD diagnosis will be extracted from medical records at 12-month follow-up and recorded on the Assessment & Diagnosis form (Appendix 1). In case it is not possible to access a child's medical record, information will be collected directly from a parent (via a phone call). A presence of ADHD diagnosis will be coded as 1 and absence as 0. In addition, if other diagnosis has been given, information about the type of diagnosis will be recorded for descriptive purposes.

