|  |  | Outcomes:                                                  | 
Primary: Parent-reported mean child behaviour problems measured with the eight-item ODD subscale of the Swanson Nolan and Pelham Rating Scale (SNAP-IV).
 
Secondary:
 
 
Mean parent-rated child hyperactivity/impulsivity and inattention measured with the respective subscale of the SNAP-IV.
 
Parenting style measured with two subscales of The O'Leary Parenting Scale.
 
Parenting satisfaction and efficacy measured using the Parental Sense of Competence scale.
 
Parenting-related strain measured with the Caregiver Strain Questionnaire.
 
Child-parent closeness measured with a subscale from the Child-Parent Relationship Scale.
 
Children's and parents' health-related quality of life. The former will be measured with the Child Health Utility measure (CHU9D) and the latter with the EQ-5D-5L.
 
 
Exploratory:
 
 
Mean rating of child oppositional and defiant speech during an online parent-child drawing task, Etch-a-Sketch Online, measured with independent observer ratings on Childhood Oppositional and Defiance Speech Sample Scale.
 
Mean parent-rated child emotional problems measured with the respective subscale of the Strengths and Difficulties Questionnaire.
 
Whether children had received a diagnosis/been prescribed medication by 12 months follow up.
 
 |

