### **5.3 Exploratory objectives**

1. To test whether STEPS reduces independently rated levels of child oppositionality and defiance expressed in speech during a period of task-focused parent-child interaction at 3- and 12-month follow-up, as compared to WAU.
2. To examine whether STEPS reduces the severity of parent-rated emotional problems at 3- and 12-month follow-up, as compared to WAU.

3. To conduct an exploratory post-randomisation effect modifier analysis to examine whether app usage levels and patterns up to 3-months influences the effect of STEPS on the primary behaviour problems outcome at 3-months and the secondary behaviour problems outcome at 12-months.
4. To conduct an exploratory post-randomisation effect modifier analysis to see whether contact within clinical services outside of the service that the child had been referred to up to 3-months influences the effect of STEPS on the primary behaviour problems outcome at 3-months, and if such clinical contact up to 12-months influences the effect of STEPS on the behaviour problems secondary outcome effect at 12-months.
5. To conduct an exploratory analysis to see if STEPS reduces the likelihood of a clinical diagnosis being made and medication prescribed by the 12 months follow up.

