## 19. Statistical analysis

### 19.1 *Clinical effectiveness*

**Does STEPS reduce the average levels of *parent-rated* child behaviour problems in children screened positive for high levels of hyperactivity/impulsivity, inattention, and conduct problems, measured over a three- (primary outcome and timepoint), six-, nine- and 12-month (secondary outcomes) period, when compared to Wait-As-Usual (WAU)?**

**Does STEPS reduce the average levels of parent-rated child hyperactivity/impulsivity and inattention screened measured over a three- and 12-month (secondary outcomes) period, when compared to WAU?**

**Does STEPS improve the average levels of: parenting style, satisfaction and efficacy, and child-parent closeness; and reduce parental strain (additional secondary outcomes) in parents of children screened positive for high levels of hyperactivity/impulsivity, inattention, and conduct problems, measured over a three- and 12-month period, when compared to WAU?**

**EXPLORATORY 1: Does STEPS reduce the average level of children's oppositional and defiant speech measured by CODSS during an online child-parent interaction task (ESO) at 3- and 12-months post-randomisation, as compared to WAU?**

**EXPLORATORY 2: Does STEPS reduce the average level of children's emotional problems measured at 3- and 12- months post-randomisation, as compared to WAU?**

**EXPLORATORY 3: Does STEPS reduce the reduces the likelihood of a clinical diagnosis being made and medication prescribed by the 12 months follow up, as compared to WAU?**

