The main analysis will follow the intention to treat (ITT) principle as much as possible (Sullivan et al., 2018; White et al., 2012). A mixed effects linear analysis of covariance (ANCOVA) model with repeated measures will be used with the SNAP-IV ODD scores at three (primary outcome), six, nine and 12 months (secondary outcomes) post-randomisation as the dependent variables, and intervention group, time point, intervention group by time point interaction, baseline SNAP-IV ODD score, and the trial centre stratification variable as independent variables, with the interaction term used to extract the primary and secondary outcome STEPS vs WAU mean differences and associated 95% confidence intervals at the four time points. Similar statistical models will be used to test for intervention effects on the other continuous secondary and exploratory outcome scale scores (average levels of directly observer-rated child behaviour problems (ESO), parent-rated hyperactivity/impulsivity and inattention, parenting style, satisfaction and efficacy, child-parent closeness and parenting-related strain) with the scores extracted at the timepoints listed in section 10 'Measures and outcomes'. For the binary exploratory diagnosis and medication outcomes we will use modified Poisson regression with robust standard errors to estimate STEPS vs WAU relative risks (and associated 95% confidence intervals) for getting a diagnosis and being prescribed medication (Zou, 2004).

In addition to ITT analysis, we will undertake a complier average causal effect (CACE) sensitivity analysis (Angrist, Imbens, & Rubin, 1996; Dunn et al., 2015) on the ODD outcome primary outcome at 3 months (T2) and ODD secondary outcome at 12 months (T5), to estimate treatment effects in those who completed at least two modules of the STEPS app (i.e., those that complied with the intervention).

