**4. Date of diagnosis: dd/mm/yyyy**

**5. Has the child received another diagnosis?**

Autism spectrum disorder (ASD)

Conduct disorder

Oppositional defiant disorder

Other

No diagnosis

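### The 12-month diagnosis outcome is named as a clinical diagnosis in five places but coded for ADHD only, and the form skips other diagnoses in assessed children without ADHD

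*Protocol*

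**What the plan says.** Five places in the protocol name the event without limiting it to ADHD:

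- Synopsis, exploratory objectives, and section 5.3, objective 5, in the same words: "STEPS reduces the likelihood of a clinical diagnosis being made and medication prescribed by the 12 months follow up".
- Synopsis, exploratory outcomes: "Whether children had received a diagnosis/been prescribed medication by 12 months follow up".
- Section 19.1, question EXPLORATORY 3: "likelihood of a clinical diagnosis being made and medication prescribed by the 12 months follow up, as compared to WAU".
- Section 19.1, the modified Poisson model: "relative risks (and associated 95% confidence intervals) for getting a diagnosis and being prescribed medication".

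Section 10.3.5, headed as clinical diagnosis and marked as an exploratory risk ratio at T5, gives the coding rule: "A presence of ADHD diagnosis will be coded as 1 and absence as 0". It then adds: "if other diagnosis has been given, information about the type of diagnosis will be recorded for descriptive purposes".

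The Assessment & Diagnosis form in Appendix 1 collects the data. Question 3 asks about an ADHD diagnosis. *Yes* leads to question 4 (date) and on to question 5. *No* leads straight to question 6 (treatment). Question 5 is the only one on other diagnoses; its options include autism spectrum disorder, conduct disorder and "Oppositional defiant disorder".

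**The concern.** The stated event and the coded event are different outcomes. A reader of the objective expects a risk ratio for receiving a clinical diagnosis; the planned variable yields one for receiving an ADHD diagnosis. The gap matters in this population. Entry requires a positive conduct screen as well as a hyperactivity screen, the synopsis gives the condition under investigation as behavioural problems, and the primary outcome is an oppositional-defiant subscale. Diagnoses other than ADHD are therefore foreseeable at 12 months.

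The form adds a second problem. Section 10.3.5 undertakes to record other diagnoses descriptively, but the routing omits them in assessed children who did not receive an ADHD diagnosis. These are the children on whose coding the two wordings can differ. As routed, the form can neither supply the promised description for them nor answer the objective as worded.

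**Working it through.** **Plan's own figure.** None is stated for this outcome. The only related figure is the sample size, set on the SNAP-IV ODD score. With d = 0.4, two-sided alpha 0.05 and 90% power, n per arm = 2 × (1.960 + 1.282)² / 0.4² = 131.3, rounded up to 132. With 25% drop-out, 132 / 0.75 = 176 per arm, or 352 in total. That reproduces section 13, and nothing below changes it.

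**Classification of an assessed child at 12 months**

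| Diagnoses received | Event as worded in the five places | Code under 10.3.5 | Other diagnosis captured by the form |
|---|---|---|---|
| ADHD only | yes | 1 | not applicable |
| ADHD and another | yes | 1 | yes (question 5 reached) |
| Another, no ADHD | yes | 0 | no (question 5 skipped) |
| None | no | 0 | not applicable |

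The wordings disagree only in the third row, and that is also the row where the form loses the information.

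**Illustration of size.** Every rate here is an assumption. Let pA be the control-arm proportion with an ADHD diagnosis (20% to 60%), let the ADHD risk ratio be 0.75, and let q be the proportion of children without ADHD who receive another diagnosis, equal in both arms (5% to 30%). Then:

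- control arm, any diagnosis: c = pA + (1 − pA)q
- STEPS arm, any diagnosis: t = 0.75pA + (1 − 0.75pA)q
- risk ratio for any diagnosis: t / c
- control children changing from 0 to 1: 176 × (1 − pA)q

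| pA | q | c | t | t / c | Children changing, of 176 |
|---|---|---|---|---|---|
| 20% | 5% | 0.240 | 0.193 | 0.80 | 7.0 |
| 20% | 30% | 0.440 | 0.405 | 0.92 | 42.2 |
| 60% | 5% | 0.620 | 0.478 | 0.77 | 3.5 |
| 60% | 30% | 0.720 | 0.615 | 0.85 | 21.1 |

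The coding in 10.3.5 gives 0.75 throughout. The objective's wording gives about 0.77 to 0.92, with roughly 4 to 42 control children classified differently. The table shows that the two are not interchangeable; it does not predict what the trial will find.

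**The case against.** The strongest reply is that the protocol has one explicit coding rule and no competing one. None of the five general phrases says that any diagnosis counts or names another disorder. The trial title concerns ADHD referrals, the exclusion criterion in 8.2 refers to a clinical diagnosis of ADHD, and question 3 of the form asks about ADHD. On this view the general wording is shorthand, and an analyst following 10.3.5 would not be in doubt. Most of this stands: ADHD-only coding is probably what was intended. The five statements of the outcome then mislabel it, and the form routing still conflicts with 10.3.5 itself.

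Three stronger readings are tempting, and the documents do not support them.

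- A reader might infer that every child with an oppositional, conduct or autism diagnosis is scored as undiagnosed. Only those without an ADHD diagnosis are; a child with both is coded 1.
- A reader might see a contradiction with section 10.3.6, where medication for neurodevelopmental and mental health disorders in general is counted. These are two separate binary outcomes, and nothing requires the same scope.
- A reader might conclude that a real effect of STEPS on other diagnoses would be hidden, so that an any-diagnosis model is required. Suppose 30% have ADHD in both arms, a further 20% of controls have another diagnosis only, and STEPS halves the latter. The risk ratio is then (0.30 + 0.10) / (0.30 + 0.20) = 0.80, against 1.00 under 10.3.5. But the halving is pure assumption, and oppositional behaviour is already measured directly as the primary outcome. Section 8.2 excludes prior ADHD diagnosis but not other prior diagnoses, and the form does not date the latter. An any-diagnosis count would therefore include diagnoses made before randomisation, which STEPS cannot affect.

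**Conclusion.** The protocol is wrong as written on this point, and the point is minor. The event named in five places is broader than the variable in 10.3.5, and the Appendix 1 routing prevents other diagnoses from being recorded in assessed children without an ADHD diagnosis, contrary to 10.3.5. Both conclusions rest on the text alone.

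The numerical size is unknown because the protocol gives no diagnosis rates; the range of 0.77 to 0.92 against 0.75 depends wholly on the assumptions stated with it. The outcome is exploratory, and neither the primary analysis nor the sample of 352 is affected. The documents do not show that the authors would misreport the result, only that the present wording would allow it.

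**What to change.** 1. Write *ADHD diagnosis* in all five places: the synopsis exploratory objective, the synopsis exploratory outcome, section 5.3 objective 5, and in section 19.1 both EXPLORATORY 3 and the modified Poisson sentence. The coding in 10.3.5 stays as it is.
2. In Appendix 1, route *No* at question 3 to question 5, so that other diagnoses are recorded for every assessed child, as 10.3.5 says.

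An any-diagnosis model is optional. If one is added, it should count only diagnoses made after randomisation, the form should record their dates, and the model should be labelled exploratory.

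The cost is five wording changes and one change of form routing. Recruitment starts in January 2022 and this protocol version is dated July 2022, so by the protocol's own dates no 12-month extraction was yet due and no collected data would need to be revisited. The optional model would cost an extra date field and one further exploratory comparison.

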### **10.3.6 Pharmacological treatment**

*Risk ratio at T5 as exploratory outcome.*

Information about any pharmacological treatment for neurodevelopmental and mental health disorders will be extracted from medical records at 12-month follow-up and will be recorded on the Assessment & Diagnosis form (Appendix 1). In case it is not possible to access a child's medical record, information will be collected directly from a parent (via a phone call). A presence of pharmacological treatment will be coded as

1 and absence as 0. If pharmacological treatment has been prescribed, information about the name of the drug and dose will be recorded for descriptive purposes.

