## **8.2 Exclusion Criteria**

- Child living under local authority care; confirmed through screening medical records.
- Child already received a clinical diagnosis of ADHD and/or received treatment for ADHD (pharmacological or non-pharmacological); confirmed either through screening medical records or discussion with parents.

If two children from the same family are referred during the trial at the same time and both meet inclusion criteria, then only the older of the two will be included. If they are referred at different times the first child will be included.

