## **10.4 Economic measures**

### **10.4.1 Resource-use data**

*T1, T2, T3, T4 and T5; (i) up to T2 and (ii) up to T5 contact with clinical services post-randomisation effect modifier for ODD at (i) T2 primary outcome, (ii) T5 secondary outcome.*

This will be measured using the Child and Adolescent Service Use Schedule (CA-SUS; Barrett et al., 2012), a measure applied in a range of populations of young people with mental health problems. The CA-SUS collects information on the use of all hospital and community-based health services, social care and education services, service-provided accommodation (for example, Local Authority foster or residential care), and prescribed medications for mental health conditions.

The format of the variable(s) that will be used as the effect modifier has not been yet finalised. Likely options include: hospital or community appointments related to mental health, therapy or counselling, dietician/nutritionist appointment, neurofeedback, family support worker, voluntary helpline and parent training classes (e.g., Incredible Years Parent Training, Triple P, 1-2-3 Magic, Empowering Parents, Empowering Communities) or parent support groups. We will aim to specify this in a future protocol amendment, and/or the statistical analysis plan.

The electronic version of this document is the latest version. It is responsibility of the individual to ensure that any paper material is the current version. Printed material is uncontrolled documentation.

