## **13. Sample size**

A total of 352 parents and their children will be recruited into the study. This power calculation is based on projected effects at the primary endpoint (3 months post-randomisation). As behaviour problems measured with the ODD subscale of the SNAP-IV questionnaire (Swanson et al., 2001) is our primary outcome, we estimated the smallest difference of clinical importance between STEPS and WAU to be equivalent to an effect size  $d = 0.4$  standard deviations based on the NICE guidance supporting the use of PT for the treatment of ODD or conduct disorder (Lundahl, Risser, & Lovejoy, 2006). A within trial drop-out rate of 25% is assumed. This is higher than in most previous trials of face-to-face PT programmes because of the unsupported nature of STEPS in OPTIMA. We will monitor drop-out rates during the internal pilot and, if necessary, recalculate the sample size if it is higher than the 25% estimated. Using Stata (version 14.0) command *sampsi*, ANCOVA analysis with a conservative zero correlation assumed between baseline and primary endpoint SNAP-IV ODD score, a two-sided test and an alpha of 0.05, we estimated that 176 individuals will be needed per trial arm (total n = 352) to provide 90% power to test the hypothesis that STEPS is superior to WAU.

[figure not shown]

Figure 1. OPTIMA enrolment, group allocation and follow-up flowchart.

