**6. Has the child received treatment?**

No treatment

Yes, medication (Go to Q7)

Yes, psychological treatment for the child

Yes, parenting support

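### The 12-month medication outcome has no start-date rule and is wider than the ADHD-only exclusion, so a drug begun before randomisation can count as an event and dilute the exploratory relative risk

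*Protocol*

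**What the plan says.** The fifth exploratory objective (Protocol 5.3) asks whether STEPS lowers the likelihood of a "clinical diagnosis being made and medication prescribed by the 12 months follow up". For the medication half, section 10.3.6 states: "Information about any pharmacological treatment for neurodevelopmental and mental health disorders will be extracted from medical records at 12-month follow-up". Presence is coded 1 and absence 0; drug name and dose are kept for description only. If the record cannot be reached, the parent is asked by phone.

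On prior treatment, section 8.2 is narrower. It excludes a child who already has an ADHD diagnosis or has "received treatment for ADHD (pharmacological or non-pharmacological"). It does not mention drugs for other conditions.

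The Assessment & Diagnosis form in Appendix 1 carries the outcome. Question 1 asks whether the service the child was referred to has formally assessed the child, and a negative answer closes the form. The form takes a date for the assessment and a date for the ADHD diagnosis. Question 6 then asks "Has the child received treatment", with no time window, and question 7 takes the drug name and dose, with no date.

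Section 19.1 analyses the result by modified Poisson regression as a relative risk and mentions no baseline medication. Separately, the CA-SUS (10.4.1), completed at T1 to T5, records "prescribed medications for mental health conditions", but the protocol does not link it to this outcome.

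**The concern.** For diagnosis, exclusion and outcome match: both concern ADHD, so a diagnosis found at 12 months should be new. For medication they do not match. The outcome covers any neurodevelopmental or mental health drug, while the exclusion removes only children treated for ADHD.

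A child on a drug for another such condition can therefore be randomised and later scored as prescribed medication, although the prescription predates the trial. The objective is about preventing prescriptions, and that one was beyond the reach of the intervention.

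Two results would suffer. The proportion prescribed medication would be overstated in both arms, and the relative risk would lie nearer 1 than the relative risk for new prescriptions.

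**Working it through.** **The plan's own figure.** The protocol gives no event rate, power or sample size for the medication outcome. Its only sample-size figure is for the primary outcome (section 13): d = 0.4, "a two-sided test and an alpha of 0.05", 90% power, zero baseline correlation and 25% drop-out. This gives 132 per arm, then 132 / 0.75 = 176 per arm, or 352 in total. The stated figure is reproduced and this point does not affect it.

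**Can a drug that predates randomisation be counted?**
- Eligibility (8.2): a non-ADHD drug does not exclude.
- Scope and coding (10.3.6): any neurodevelopmental or mental health drug, presence = 1, no start date.
- Timing (5.3 and synopsis): an upper limit of 12 months and no lower limit.
- Form (Appendix 1): reached only if the child was assessed; no time window at question 6; no date at question 7.

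So it can, through the form, for a child who was assessed. Nothing in 10.3.6 or on the form tells the person coding to leave it out.

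**Size.** The documents give no prevalence of baseline medication and no prescribing rates, so every input here is an assumption: new-prescription risk r0 = 20% under WAU and r1 = 12% under STEPS (true relative risk 0.60), and prevalent use p0 equal in both arms.

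If every prevalent user is counted:
coded RR = [p0 + (1 − p0) r1] / [p0 + (1 − p0) r0]

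If half the children are assessed, prevalent use is unrelated to being assessed, and new prescriptions arise among assessed children:
coded RR = [0.5 p0 + (1 − p0) r1] / [0.5 p0 + (1 − p0) r0]

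| p0 | All counted | Half assessed |
|---|---|---|
| 2% | 0.138 / 0.216 = 0.64 | 0.128 / 0.206 = 0.62 |
| 5% | 0.164 / 0.240 = 0.68 | 0.139 / 0.215 = 0.65 |
| 10% | 0.208 / 0.280 = 0.74 | 0.158 / 0.230 = 0.69 |
| 15% | 0.252 / 0.320 = 0.79 | 0.177 / 0.245 = 0.72 |

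**Sensitivity to the assumed rates**, with all prevalent users counted. With 20% under WAU and a true relative risk of 0.70, p0 of 2%, 5% and 10% gives 0.73, 0.76 and 0.81. Approximate power with 176 per arm falls from 32% to 29%, 26% and 21%. Across WAU risks of 10% to 30% and p0 of 2% to 10%, a true 0.50 becomes 0.53 to 0.76 and a true 0.70 becomes 0.72 to 0.86. With p0 = 0, which is what a post-randomisation definition achieves, the true value is recovered.

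**The case against.** **The form filters.** A reader might infer that every child already on a qualifying drug is scored 1 whatever happens in the trial. The documents do not support that. Question 1 closes the form for unassessed children, so prevalent users among them never reach the treatment question. Section 9.4 expects no assessments in the first three months, and the protocol does not say how many children will be assessed by 12 months. This stands, and is why the second column of results is shown.

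**Question 6 may mean treatment after assessment.** Question 3 asks about diagnosis after the assessment, and the objective reads naturally as a new event. That reading is open, but question 6 does not state it and 10.3.6 has no such limit. The text is ambiguous, and the literal coding rule points the other way.

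**Chance imbalance.** A reader might add that unequal numbers of prevalent users in the two arms would pass as a treatment effect. This is no separate bias: randomisation balances prior use in expectation, and the planned confidence interval already reflects chance differences.

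**The analysis plan could deal with it.** Restricting to non-users or adjusting for baseline medication is ordinary analysis-plan detail, and the T1 CA-SUS would help. This stands in part. However, the protocol itself fixes the 0/1 coding, its outcome form holds no medication date from which to apply a cut-off, and the CA-SUS wording covers mental health conditions without naming neurodevelopmental disorders.

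**Conclusion.** The point holds in a limited form. Exclusion and outcome differ in scope, and neither 10.3.6 nor Appendix 1 separates drugs started before randomisation from those started after. As written, the rule can count events that STEPS could not prevent, which does not fit the objective.

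The consequence is dilution towards 1, on average without favouring either arm. The documents support no claim of a systematic advantage for STEPS or WAU. Under the assumed 20% and 12% risks, the relative risk of 0.60 becomes 0.64 to 0.79 if all prevalent users are counted and about 0.62 to 0.72 if half are assessed, for prevalent use of 2% to 15%. The real prevalence is not given and may be small.

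Severity is low: this is one half of an exploratory objective and bears on neither the sample size nor the primary and secondary effectiveness analyses.

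**What to change.** 1. In 10.3.6, define the event as a drug for a neurodevelopmental or mental health disorder first prescribed after the date of randomisation.
2. Add a medication start date at Appendix 1 question 7, taken from the same record review, or from the parent where the phone fallback is used.
3. Use the T1 CA-SUS as a supporting source and report baseline use by arm. Because its wording may not cover every drug within the outcome's scope, the start date should be the main source.

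Eligibility does not change. The cost is one sentence of definition and one field from a record that is already being read, with no extra participants or visits.
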